**Figure 5 F5:**
[figure not shown]
**One leg neuromuscular training associated with strengthening exercises. A)** One-leg balance with knee extension, on stable terrain; **B** and **C)** One-leg balance at 30° of knee flexion, on stable and unstable terrain, respectively; **D)** Unipodal squat. These activities should keep the pelvis balanced and avoid excessive pronation of the foot.

One-leg balance with knee flexion (2nd-3rd weeks): The patient stood on one foot with the knee at 30° flexion, keeping the leg of the support limb perpendicular to the ground and the hip and trunk slightly flexed. The patient was asked to hold this position, keeping their balance and avoiding compensatory movements such as rotation and inclination of the trunk and pelvis, adduction and medial rotation of the hip or pronation of the support foot. In the second week, the patient performed this exercise on a flat surface (Figure 5B) whereas in the third week, it was done on an unstable surface (Figure 5C).

One Leg Squat (4th week): The patient stood on one foot with the knee extended and the hip, pelvis and trunk in a neutral position. They were asked to squat slowly until the knee reached 30° of flexion. The patient was then asked to squat while flexing the hip and trunk more, keeping the leg of the support limb perpendicular to the ground and avoiding compensatory movements such as rotation and inclination of the trunk and pelvis, adduction and medial rotation of the hip or pronation of the foot (Figure 5D).

All patients allocated to this group received detailed explanations of the movement disorder that they exhibited when they performed weight-bearing activities (ipsilateral trunk lean and contralateral pelvic drop, hip adduction and medial rotation and foot pronation) [11]. They were also informed how to correct this abnormality while performing the exercises and were verbally stimulated by the therapist. All exercises were performed in front of a mirror in order to provide visual feedback. The patients performed three sets of each exercise (one-minute intervals between sets), with 15 repetitions. Similar to the CG, the resistance was increased at the moment when the exercise became easy to perform. The correction of body sway exercises was also conducted in sets of three and held for the following period of time: 20 seconds in the first week; 30 seconds in the second week and 40 seconds in the third week.

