### Primary outcomes

The primary outcome was functional capacity, measured after treatment (4 weeks) using the Anterior Knee Pain Scale – AKPS [30].

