### Secondary outcomes

The secondary outcomes were pain intensity, muscle strength of the hip abductors and lateral rotators, extensors of the knee and three-dimensional kinematics of the trunk, pelvis, hip, knee and ankle during the step down test, measured after treatment (4 weeks). In addition, functional capacity and pain intensity were assessed three and six months after randomization.

The description of each of these measurements is described below.

**Anterior Knee Pain Scale – AKPS**: This is a specific questionnaire for anterior knee pain, composed of 13 items that are separated in categories that involve different levels of knee function. Each item was answered and the total result was added to a global index with a maximum score of 100 points, which represents “no deficit”, and a minimum score of zero, representing “the highest possible deficit” [30,34].

**Numerical Pain Rating Scale - NPRS**: This scale measures pain intensity. The score ranges from 0 to 10 points, with 0 representing a “complete absence of pain” and 10 representing the “worst possible pain” [30]. The patients were asked to classify their pain intensity based on the last seven days and while performing the step down test.

**Manual Dynamometer (Lafayette Instrument Company, Lafayette, IN):** This tool is used to quantify muscle strength during maximum voluntary isometric contraction, with adequate reliability in both inter and intra-assessments [32,33]. The abductors, lateral rotators and extensors of the hip and the knee extensors were assessed as described by Bolgla et al. (2011).

**Kinematic Analysis of the Step Down Test:** The Vicon-Nexus® system was used, which involves 8 infrared cameras capable of 250 frames per second (fps) and a resolution of 1MP 1024×1024. This system captured the movements of the reflective markers that were placed on specific anatomical points of the patient’s skin, based on the Vicon® Plug in Gait model [35,36]. All of the cameras were connected to a computer dedicated to treatment of the video signal, which had different functions: timing circuit/control; coordinate generating circuit and interface circuit of the cameras. Once stored in the video memory, the data were transferred to a second general purpose computer. Vicon-Nexus® software was used to process and reconstruct 3D images of the markers through a biomechanical model and a number of mathematical algorithms.

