### Data analysis

The normality of the data will be confirmed by a visual inspection of the histograms. A logarithmic transformation [log(x + 1)] for the complete set of data will be used for the variables of asymmetric distribution. In cases where non-parametric distribution persists, all comparisons will be performed with the raw data (without transformation), using the non-parametric tests. The effects of the interventions (between-group differences) will be calculated using linear mixed models by using interaction terms (group allocation versus time), which is equivalent to the between-group differences. The within-group differences will be calculated using repeated measures ANOVA. P-values < 0.05 will be considered as statistically significant. The data will be double checked before analysis. The Statistical Package for the Social Sciences (SPSS) software was used for all analysis.

The clinical relevance of the results will be confirmed by calculating the effect size (Cohen *d*) of the significant differences found between the assessments. The following effects will be considered: 0.00-0.49 small; 0.50-0.79 medium and above 0.80 great (Cohen, 1988).

The calculation of the sample size was performed to detect a difference of 8 points on the Anterior Knee Pain Scale (AKPS) (with a standard deviation estimated at 7.5 points). The alpha level was 0.05 and the statistical power was 80%. Therefore, the sample size required (per group) was 15. We decided to increase the sample to compensate for the loss of patients or to compensate for abnormally distributed data. Each group was increased to 17 (i.e. total sample size of 34 participants).

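### One unadjusted 0.05 rule covers all the secondary outcomes, and significance then triggers the effect-size step that is meant to confirm clinical relevance

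*Protocol article*

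**What the plan says.** All of this is in the protocol article.

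- **Primary outcomes:** "The primary outcome was functional capacity, measured after treatment (4 weeks) using the Anterior Knee Pain Scale – AKPS". There is one outcome at one time point.
- **Secondary outcomes:** the 4-week list begins with "pain intensity, muscle strength of the hip abductors and lateral rotators, extensors of the knee". The movement analysis, also at 4 weeks, is described as "three-dimensional kinematics of the trunk, pelvis, hip, knee and ankle during the step down test". For the later visits, the section states that "functional capacity and pain intensity were assessed three and six months after randomization". The dynamometer paragraph adds a muscle group: "The abductors, lateral rotators and extensors of the hip and the knee extensors were assessed". The NPRS paragraph has two pain ratings, one for the past week and one during the step down test.
- **Data analysis:** "P-values < 0.05 will be considered as statistically significant". The sentence is not limited to the primary outcome. The section orders no outcomes, adjusts for no multiplicity and does not mark secondary results as exploratory. Between-group effects come from the group-by-time terms of linear mixed models, and within-group changes from repeated measures ANOVA. Cohen d is then calculated for the significant differences to confirm clinical relevance, in bands of small (up to 0.49), medium (0.50 to 0.79) and great (above 0.80).
- **Intervention/control:** the experimental group is taught to correct named movement faults, "ipsilateral trunk lean and contralateral pelvic drop, hip adduction and medial rotation", and the list goes on to foot pronation. The analysis does not use this list to focus the kinematic comparisons.

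**The concern.** Two stated rules act together. The first gives every secondary comparison the same significance label as the primary one. The second uses that label to decide which results receive an effect size and a statement about clinical relevance. With many comparisons on 34 women, some isolated kinematic, strength or pain differences can be expected to cross 0.05 by chance.

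A relevance check should screen such results out. Here it sees only results that have already passed the significance filter, and in a trial this small those results have large observed effects almost by construction. At stake is the reading of the secondary results: a chance difference could be published as significant and clinically relevant in a trial whose Discussion hopes to guide physical therapists' decisions.

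**Working it through.** **1. The plan's own figure.** The inputs from Data analysis are a difference of 8 points, SD 7.5, alpha 0.05 (taken as two-sided) and power 80%. The normal approximation gives n = 2 × (1.96 + 0.84)² × (7.5/8)² ≈ 13.8, so 14 per group. With the noncentral t distribution, power is 77.5% at 14 and 80.5% at 15 per group. The stated 15 is reproduced. It concerns a single test, the primary one.

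**2. Number of secondary between-group comparisons.** The article gives no count. The kinematic figure assumes one variable per plane: 5 segments × 3 planes = 15.

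| Component | Lower count | Upper count |
|---|---|---|
| Kinematics, 4 weeks | 15 | 15 |
| Strength, 4 weeks | 3 | 4 (with hip extensors) |
| Pain, 4 weeks | 1 | 2 (two ratings) |
| Pain, 3 and 6 months | 2 | 4 (two ratings) |
| AKPS, 3 and 6 months | 2 | 2 |
| Total | 23 | 27 |

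The lower count plus hip extensors gives 24, the working figure below. The within-group ANOVAs fall under the same rule but are not counted.

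**3. False positives if no secondary effect exists.**

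- Expected number = m × 0.05: 23 × 0.05 = 1.15; 24 × 0.05 = 1.2; 27 × 0.05 = 1.35. Correlation does not change these.
- Chance of at least one if independent = 1 − 0.95^m: 69.3% for 23, 70.8% for 24, 75.0% for 27.

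**4. Effect of correlation.** The outcomes are measured on the same women, so the tests are correlated; the article gives no values. Simulation of 24 equally correlated normal test statistics (200,000 draws, all nulls true) gives:

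| Correlation | 0.1 | 0.2 | 0.3 | 0.4 | 0.5 | 0.6 | 0.7 |
|---|---|---|---|---|---|---|---|
| At least one p < 0.05 | 69% | 65% | 59% | 53% | 46% | 39% | 31% |

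Interpolating between 0.4 (52.9%) and 0.5 (45.9%), the 50% line is crossed at 0.4 + 0.1 × 2.9/7.0 ≈ 0.44. The crossing is at about 0.42 for 23 tests and 0.48 for 27. With blocks for pain, AKPS, strength and kinematics (within-block/between-block correlation), the results are 64% at 0.3/0.1, 55% at 0.5/0.2, 51% at 0.6/0.2 and 44% at 0.7/0.3.

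**5. What the effect-size step can screen out.** In a simple two-group comparison, p < 0.05 requires |d| ≥ t × √(2/n).

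- 17 per group: 2.037 × √(2/17) = 2.037 × 0.343 ≈ 0.70.
- 15 per group: 2.048 × √(2/15) = 2.048 × 0.365 ≈ 0.75.

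Both lie in the plan's medium band, so any between-group difference that is significant on this basis is at least medium.

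This depends on the SD. If a change score is tested but d uses the raw-score SD, with equal variances and pre-post correlation r, the threshold becomes 0.70 × √(2(1 − r)). It falls below 0.50 when 2(1 − r) < (0.50/0.70)² ≈ 0.51, that is, when r exceeds about 0.74. The article does not say which SD is used.

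**The case against.** The strongest case against is that this is a condensed article. A list of kinematic variables and a multiplicity policy may stand in a fuller protocol or analysis plan, and nominal testing of outcomes already labelled secondary is common. The main protection is in place: one primary outcome, one time point, and a sample size calculated for it. This stands as far as an absent adjustment goes, and no finding is made of the absent variable list. It does not answer the point about what the article does fix: an unrestricted 0.05 rule and a relevance step that depends on it.

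The count is also open to challenge, and rightly. Fifteen of the 24 comparisons rest on an assumption. Measuring in three dimensions does not commit the trial to testing every plane, and the step down test sets knee flexion to about 60° for everyone, so one sagittal variable is largely fixed by design. Without kinematics, nine comparisons remain, and 1 − 0.95^9 = 37%. More variables per plane, or both limbs, would push the count the other way.

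A reader might infer that at least one false significant finding is more likely than not. The documents do not support this as a plain statement. It needs every secondary null to be true, a count near 24, and an average correlation below about 0.44. None of these can be established from the article, and adjacent joints and repeated scores in the same women will be correlated.

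**Conclusion.** The point holds in a limited form. The plan applies an unadjusted 0.05 threshold to all outcomes and lets significance decide which results have their clinical relevance confirmed. Assuming one kinematic variable per plane, there are roughly 23 to 27 secondary between-group comparisons. If none of them reflects a real effect, about 1.2 false positives are expected in 24 tests. The chance of at least one is up to about 70 to 75% under independence and is below 50% once the average correlation passes about 0.44.

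The effect-size step gives little protection: at 17 per group, a simple comparison needs d of about 0.70 to reach significance, so most chance findings would be called at least medium. The reservation is the unstated SD.

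A reader might also infer that the trial's main conclusion is at risk. It is not: the AKPS test at 4 weeks is a single test at 0.05 and its sample size reproduces. The change is worth making because it is cheap and affects how the secondary results will be read.

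**What to change.** In Data analysis:

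- Reserve the phrase *statistically significant at 0.05* for the between-group AKPS contrast at 4 weeks.
- Report all secondary outcomes as between-group differences with 95% confidence intervals, labelled supportive.
- Give effect sizes for all of them, not only the significant ones, and state which SD standardises d.

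Optionally, name in advance the kinematic variables that match all the movement faults listed under Intervention/control as the focus of the kinematic analysis: ipsilateral trunk lean, contralateral pelvic drop, hip adduction, hip medial rotation, and foot pronation where the marker model measures it. If foot pronation is left out, the reason should be given, since the article lists it with the others.

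The cost is analysis wording only, with no new data or patients. The downside is that fewer secondary results can be called significant.

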## Discussion

Although PFPS treatment with an emphasis on strengthening the hip muscles is well established in the literature and has demonstrated satisfactory results for the clinical problem and kinematic abnormalities [14,16,26,31,38], the role of neuromuscular training with an emphasis on controlling lower limb movements remains relatively unclear [19,25,41].

Mascal, Landel and Powers (2003), in a report of two cases, demonstrated an improvement in pain, kinematic changes in the lower limbs and an improvement in functional capacity during the step down test in PFPS patients who participated in a protocol of gluteal muscle strengthening and neuromuscular training. However, since it was a case-series, the results cannot be considered as robust enough for implementation in clinical practice. Recently, Salsish et al. (2012) demonstrated that voluntary alteration of lower limb movement patterns could directly affect referred pain in PFPS patients while squatting. However, the effect observed in the present study was only recorded during the execution of the movement. There is a lack of studies in the literature that adopt a neuromuscular training program to correct or reduce existing biomechanical abnormalities in patients with patellofemoral disorders, as well as studies that analyze the effect of this therapeutic method in association with other techniques that are already known. Therefore, the conclusions of the present study could provide significant information about neuromuscular training in patients with PFPS.

A greater understanding of the effects of sensory motor training on the clinical and biomechanical aspects of PFPS patients could clarify the situation and consolidate the concept of another potentially effective conservative treatment, as well as guiding physiotherapists in the clinical decision-making process for PFPS patients.

## Abbreviations

AKPS: Anterior knee pain scale; CG: Control group; EG: Experimental group; FIQ: Functional index questionnaire; NPRS: Numerical pain rating scale; PFPS: Patellofemoral pain syndrome.
